### Randomization

Investigators, outcome assessors, data analysts and participants will all be blinded to the treatment allocation via the use of an apparently identical inert placebo and a central automated allocation procedure. Participants will be stratified by practice location, systolic BP (above or below 140 mmHg) and urine albuminuria (uACR above or below 30 mg/mmol) and assigned to either active treatment or inactive placebo using a minimization algorithm with a 70:30 weighted-coined approach if there is an imbalance. Randomization assignment will be centrally generated using the PC-CRTU secured web-based randomization system.

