**Methods/design:**

STOP-CKD is a multicentre, prospective, randomized, double-blind, placebo-controlled pilot trial of 240 adult patients with stage 3 chronic kidney disease recruited from up to 20 general practices in South Birmingham, England. Participants will be randomly allocated using a secured web-based computer randomization system to receive either spironolactone 25 mg once daily or a matching inactive placebo for 40 weeks, followed by a wash-out period of 6 weeks. Investigators, outcome assessors, data analysts and participants will all be blinded to the treatment allocation. The primary endpoint is improved arterial stiffness, as measured by carotid-femoral pulse wave velocity between baseline and 40 weeks. The secondary endpoints are incidence of hyperkalaemia, change in estimated glomerular filtration rate, change in urine albumin:creatinine ratio, change in brachial blood pressure, change in pulse waveform characteristics and overall tolerability of spironolactone. An additional quality control study, aiming to compare the laboratory serum potassium results of samples processed via two methods (utilizing routine transport or centrifugation on site before rapid transport to the laboratory) for 100 participants and a qualitative research study exploring patients’ and general practitioners’ attitudes to research and the use of spironolactone in chronic kidney disease in the community setting will be embedded in this pilot study.

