### Endpoints

The primary endpoint of the study will be a change in cfPWV between baseline and 40 weeks. Secondary endpoints are: (i) change in brachial BP; (ii) change in eGFR; (iii) change in uACR; (iv) change in pulse waveform characteristics; (v) incidence of hyperkalaemia; (vi) incidence of renal dysfunction (increment of creatinine ≥30% or reduction of eGFR ≥25% from baseline); (vii) incidence of other adverse events.

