### Sample size calculation and planned statistical analysis

In our recent study of the effect of spironolactone, the Chronic Renal Impairment in Birmingham II (CRIB II) study, the standard deviation of the change in cfPWV was 1.0 m/s in the active treatment group and 0.9 m/s in the control group. Hence, 100 subjects in each arm will provide 90% power with an *α* value of 0.05 to demonstrate a difference in change of cfPWV of 0.5 m/s between the active treatment and control groups. We aim to recruit 240 patients to account for an approximate drop-out rate of 20%, which will result in at least 200 patients completing this randomized control trial, with 100 patients in each arm (inactive placebo versus spironolactone).

The difference in the primary outcome between experimental conditions will be assessed using generalized mixed models. Repeated measures within a subject will be characterized as *R* side residual over-dispersion parameters, accounting for baseline values. Frequency differences will be tested using Fisher’s exact test. A prespecified multivariable analysis will examine the influence of change in systolic BP and other relevant factors on changes in the primary endpoint. Outcomes will be analyzed using intention-to-treat analysis. A *P* value of less than 0.05 will be considered statistically significant.

Data entry, coding, security, storage, access and quality assurance will be managed according to PC-CRTU policy [54]. Study investigators will have access to the final trial dataset.

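### The primary model as stated names none of the three minimisation factors; if they predict change in cfPWV, its standard errors are too wide and its test conservative (minor)

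*Protocol article*

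**What the plan says.** **Allocation** (Randomization). "Participants will be stratified by practice location, systolic BP (above or below 140 mmHg) and urine albuminuria (uACR above or below 30 mg/mmol"), with assignment made "using a minimization algorithm with a 70:30 weighted-coined approach if there is an imbalance". The abstract gives the number of levels of the practice factor: patients are "recruited from up to 20 general practices in South Birmingham, England".

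**Endpoint** (Endpoints). "The primary endpoint of the study will be a change in cfPWV between baseline and 40 weeks".

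**Primary model** (Sample size calculation and planned statistical analysis). "The difference in the primary outcome between experimental conditions will be assessed using generalized mixed models". On its structure the text adds: "Repeated measures within a subject will be characterized as" R "side residual over-dispersion parameters, accounting for baseline values". No allocation factor and no practice effect is named.

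**Further adjusted analysis** (same section). "A prespecified multivariable analysis will examine the influence of change in systolic BP and other relevant factors on changes in the primary endpoint".

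**The concern.** Minimisation keeps the arms alike on practice, systolic BP and albuminuria. If these factors predict the outcome, the difference between arms varies less from trial to trial than it would under simple randomisation. A model that leaves them out keeps their variation in its residual, so it computes its standard error as if that variation could still fall unevenly between the arms. Intervals are then wider, and P values larger, than the design warrants.

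The multivariable analysis does not fill the gap. It is a separate analysis, and the one variable it names, change in systolic BP, is measured after randomisation and is a secondary endpoint. It is not the baseline BP category used in allocation.

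At stake is the match between design and analysis. The trial is a pilot intended to inform a definitive trial, so a correctly sized interval for the cfPWV effect has value beyond the significance test.

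**Working it through.** **Inputs from the protocol article.** SD of change in cfPWV 1.0 m/s (active) and 0.9 m/s (control); difference 0.5 m/s; 100 per arm completing; alpha 0.05 (taken as two-sided); up to 20 practices; 70:30 weighted coin.

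**Assumed, because the document gives no figure.** The share R² of outcome variance, after baseline adjustment, that the three factors explain: 0% to 40%. Patients in the upper category: 40% for systolic BP and 15% for uACR.

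**Step 1: the plan's own figure.** Pooled SD = √((1.0² + 0.9²)/2) = 0.951. SE of the difference = 0.951 × √(2/100) = 0.1345. Power = Φ(0.5/0.1345 − 1.96) = Φ(1.76) = 96.0%. The stated 90% is therefore not reproduced: 90% needs 2 × (1.96 + 1.2816)² × 0.905/0.25 = 76.1, so 77 per arm. The difference is on the safe side and is separate from this point. It does mean that power is not the pressing issue here.

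**Step 2: closed form under perfect balance.** If the factors were perfectly balanced, the true SE would be the model SE times √(1 − R²). The test without the factors would then have type I error 2(1 − Φ(1.96/√(1 − R²))):

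- R² = 0.05: 4.4%
- R² = 0.10: 3.9%
- R² = 0.20: 2.8%

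**Step 3: simulation of the stated scheme.** A 70:30 coin does not balance perfectly, so the closed form overstates the effect at larger shares. For each share, 6,000 trials were simulated with 200 patients, 20 practices, minimisation on the three factors and outcome SD 0.951. Two models were fitted: treatment alone, and treatment plus systolic BP category, uACR category and practice as fixed effects.

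| Variance explained | Type I error, factors omitted | Type I error, factors included | Model SE / true SE, omitted | Power at 0.5 m/s, omitted | Power at 0.5 m/s, included |
|---|---|---|---|---|---|
| 0% | 5.0% | 5.2% | 1.00 | 95.8% | 94.9% |
| 3% | 4.3% | 4.5% | 1.03 | 96.7% | 96.1% |
| 8% | 4.5% | 5.4% | 1.03 | 96.5% | 96.4% |
| 15% | 3.3% | 4.8% | 1.08 | 96.8% | 97.8% |
| 25% | 3.0% | 4.7% | 1.11 | 97.2% | 98.6% |
| 40% | 2.1% | 4.9% | 1.20 | 98.2% | 99.6% |

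The Monte Carlo 95% margin near 5% is 1.96 × √(0.05 × 0.95/6,000) = 0.55 percentage points. The rows for 3% and 8% therefore cannot be told apart and lie close to 5%. From 15% upward the shortfall is clear. At 40%, perfect balance would give a ratio of 1/√0.60 = 1.29; the simulated 1.20 shows how far the weighted coin dilutes the effect.

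**Simplifications.** The simulation uses a single outcome per patient, without the week 46 measurement. It treats baseline cfPWV as already adjusted for, and minimises the 200 completers directly.

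**The case against.** The strongest reply is that this is a condensed journal article, that a fuller analysis plan may list the covariates, and that nothing in the text excludes the minimisation factors. A reader might infer that the model adjusts only for baseline values of the outcome. The document says neither: it refers to baseline values without naming the variable, and a mixed model could carry a practice effect. A reader might also infer that the multivariable analysis leaves these factors out, but its open reference to other relevant factors could cover them.

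This limits how strongly the point can be put but does not remove it. The section is not silent on the model. It gives the within-subject covariance approach and one adjustment, so someone following it as written would fit a model without the factors. Whatever the multivariable analysis contains, it is a separate analysis.

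The second reply is that the factors may explain little. The endpoint is a change, and adjustment for baseline cfPWV may absorb much of any link with BP. Patients with uACR of 70 mg/mmol or more are excluded, which narrows the upper category. The device is described as not operator-dependent, and all practices are in one area, which argues against large practice effects. This stands. It makes the lower rows of variance explained plausible, and there the consequence is close to nil.

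**Conclusion.** The mismatch between allocation and stated primary model is real, and it is minor. Its effect is conditional: to the extent that practice, systolic BP and uACR predict change in cfPWV beyond baseline cfPWV, the model's standard errors are too wide and its test conservative. Over assumed shares of 0% to 40%, the ratio of model to true SE runs from 1.00 to 1.20 and type I error from 5.0% down to 2.1%. At 3% to 8% the effect is slight.

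Two stronger readings are not supported. One is that the true type I error is below 5% as a matter of fact; the document gives no variance share, and at 0% there is no effect. The other is that the trial's validity or power is threatened. No bias or false-positive risk arises, and power at 0.5 m/s is 95.8% or more without the factors in every scenario. The benefit of the change is correctly sized intervals and, if the factors are prognostic, some added precision.

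**What to change.** State in the analysis section that the primary model includes the three minimisation factors alongside baseline cfPWV, with practice as a random or fixed effect. If a separate analysis plan already says so, one sentence confirming it is enough. Whether systolic BP and uACR enter as the allocation categories or as continuous terms is the analyst's choice.

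The cost is one sentence. Practice is known at allocation; the assessment flowchart (Table 2) shows BP collected at screening and randomisation and uACR at screening. If the factors prove not to be prognostic, fitting them with 20 practices as fixed effects lowers power from 95.8% to 94.9%.

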### Unblinding

Researchers will be unblinded after the completion of 46 weeks follow-up of all subjects and closure of the trial. The practice staff and all participants involved in the study, including those who had withdrawn, will also be informed of their trial medication allocation (spironolactone or inactive placebo). During the trial, code breaking will be avoided whenever possible. If emergency unblinding is deemed to be appropriate, research team members have access to break the randomization code. When assessing severe adverse events, it will be assumed that the participants receive spironolactone (not inactive placebo). If the event is thought to be related and that the knowledge of treatment will alter the medical management, unblinding will be performed via the PC-CRTU secured web-based code-breaking system with a paper-based code-breaking system back up.

### Treatment

STOP-CKD is a double-blinded, placebo-controlled, randomized trial involving two treatment arms: spironolactone 25 mg orally once daily and inactive placebo orally once daily. All participants will receive their allocated trial medication for 40 weeks. The trial medication is supplied by an authorized trial medication manufacturing unit and funded via an NIHR Research for Patient Benefit programme grant for this study. The trial medication was labelled and packaged by the trial medication manufacturing unit prior to delivery to a designated community pharmacy hub. The trial medication will be dispensed at the pharmacy hub and delivered to the local community pharmacy closest to the recruited general practice for collection by the participants.

All participants will complete the medication monitoring questionnaire at each visit to record any side effect related to the trial medication and self-report trial medication compliance during the 40 weeks treatment phase. If participant’s serum potassium concentration is 5.5 to 5.9 mEq/l on repeat samplings, the trial medication will be reduced from once daily to once every other day (see Figure 2).

### Withdrawal criteria

Participants will be withdrawn from the trial if they choose not to continue, if their GP considers that continued participation in the trial is inappropriate or if they are no longer eligible according to the withdrawal criteria listed in Table 3. Participants who withdraw from the trial will be asked if they are willing to attend a final research visit within 7 days of stopping the trial medication for blood and urine sampling, BP and Vicorder measurement and completion of the EQ5D-5 L and medication monitoring questionnaire. Data will be collected for an intention-to-treat analysis.

**Table 3 T3:** Withdrawal criteria

**System**	**Adverse effect**	**Action**
Blood pressure	Hypotension	Withdraw trial medication if systolic blood pressure <100 mmHg or postural drop of systolic blood pressure >20 mmHg.
Metabolic	Hyperkalaemia	Withdraw trial medication if serum potassium ≥ 6 mEq/l on repeat sampling.
	Hyponatraemia	Withdraw trial medication if serum sodium <130 mEq/l on two occasions.
Renal	Renal dysfunction	Withdraw trial medication if serum creatinine increment ≥30% or eGFR reduction ≥25% from baseline.
Endocrine	Men: gynaecomastia, impotence, diminished libido	Withdraw trial medication if participant is intolerant of the side effect or effects.
	Women: hirsutism, oligomenorrhoea, amenorrhoea, menorrhagia, breast tenderness	
Nervous system	Headache	Withdraw trial medication if symptom persists for >1 week.
	Confusion, ataxia, drowsiness	Check postural blood pressure and serum sodium level. If postural blood pressure and serum sodium levels are within normal levels, but symptoms persist for >1 week, withdraw trial medication.
	Lethargy	Withdraw trial medication if symptom persists for >1 week.
Dermatological	Rash	Withdraw trial medication.
	Lichen planus, lupus-like syndrome	Withdraw trial medication.
Hypersensitivity	Anaphylaxis, contact dermatitis, eosinophilia	Withdraw trial medication immediately.
Gastrointestinal	General abdominal discomfort	Withdraw trial medication if persistent discomfort for >1 week.
	Diarrhoea or vomiting	Withdraw trial medication if persistent diarrhoea or vomiting for >3 days.
	Gastric or duodenal ulcer or bleeding	Withdraw trial medication.
Haematological	Agranulocytosis	Withdraw trial medication.
Hepatic	Hepatotoxicity (alanine transferase > 123 U/l or bilirubin > 44 μmol/l)	Withdraw trial medication.
Oncological	Animal studies suggested association between spironolactone with benign adenoma of the thyroid and testes, malignant breast tumours, hepatocellular carcinoma and leukemia	Withdraw trial medication.

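### Meeting a Table 3 drug-stopping criterion is treated as leaving the trial, so no week-40 cfPWV is planned for those participants although the analysis is to be by intention to treat

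*Protocol article*

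**What the plan says.** The Withdrawal criteria section gives three routes out of the trial: the participant's own choice, the GP's judgement, and Table 3. It opens "Participants will be withdrawn from the trial if they choose not to continue" and ends its list with participants leaving "if they are no longer eligible according to the withdrawal criteria listed in Table 3".

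Table 3 itself is narrower. Each of its actions concerns the medication, for example "Withdraw trial medication if serum potassium ≥ 6 mEq/l on repeat sampling" and "Withdraw trial medication if serum creatinine increment ≥30% or eGFR reduction ≥25% from baseline". No row removes the participant from the trial.

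For those who are withdrawn, the section describes one further contact: they "will be asked if they are willing to attend a final research visit within 7 days of stopping the trial medication". Besides blood and urine samples, that visit covers "BP and Vicorder measurement and completion of the EQ5D-5 L and medication monitoring questionnaire". No later visit is described for them.

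The primary endpoint is change in cfPWV from baseline to week 40 (Endpoints). cfPWV is scheduled at randomization, week 40 and week 46 only (Design; Table 2). The statistical section states "Outcomes will be analyzed using intention-to-treat analysis", and the Withdrawal criteria section gives the same purpose for the data it collects.

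**The concern.** Stopping a drug and leaving a trial are different events. An intention-to-treat comparison at week 40 needs the week-40 outcome of people who stopped early as well as those who did not. Here the text turns the first event into the second, and the visit it offers is optional and tied to the date of stopping, which may be as early as the first weeks.

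The loss is unlikely to be neutral. The Background names hyperkalaemia and worsened renal function as physicians' concerns with this drug class, and both are Table 3 triggers. More participants could therefore be lost on spironolactone than on placebo, for reasons connected with treatment. What is at stake is which effect the primary analysis estimates: that in everyone randomised, or that in people who could stay on the drug. A pilot meant to inform a definitive trial in primary care needs to know which of the two it has.

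**Working it through.** **1. The passages side by side**

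- Withdrawal criteria, text: a Table 3 criterion means withdrawal from the trial.
- Table 3: the same criterion means withdrawal of trial medication.
- Withdrawal criteria, text: one voluntary final visit, within 7 days of stopping, with cfPWV.
- Follow-up visits: all participants attend week 46. The same paragraph has all participants stop the trial medication at week 40 with a pill count, which describes people still on drug.
- Unblinding: refers to 46 weeks of follow-up of all subjects. The next sentence mentions withdrawn participants separately, and sets no visit for them.

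The last two items do not say whether participants withdrawn under Table 3 are covered. On the text as it stands, a withdrawn participant has either no cfPWV after baseline, or one reading close to the stopping date.

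**2. The plan's own power figure**

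Inputs (Sample size section): SD of change 1.0 and 0.9 m/s, difference 0.5 m/s, alpha 0.05 (two-sided assumed), 100 per arm, 90% power.

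Pooled SD = √((1.0² + 0.9²)/2) = √0.905 = 0.951.

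Power = Φ(δ / (SD × √(2/n)) − 1.96) = Φ(0.5 / (0.951 × 0.1414) − 1.96) = Φ(1.76) = 96%.

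With SD 1.0 it is 94%. The stated 90% is not reproduced, but the departure is on the conservative side and is a separate matter.

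**3. What loss of values does to power**

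If 20% or 30% of 120 per arm have no week-40 value and the effect stays at 0.5 m/s, 96 or 84 per arm remain, and power is 95% or 93%. Precision is not the problem. Bias, and which effect is estimated, are.

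**4. What early stopping does to the effect (illustration)**

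The documents give no stopping rate and no rate of offset, so both are assumptions. Let p be the share of the spironolactone arm that stops and r the effect those people keep at week 40.

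Effect in all randomised = (1 − p) × 0.5 + p × r.

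With r = 0 and 120 per arm followed to week 40:

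| p | All randomised (m/s) | On-drug only (m/s) | Power, SD 0.951 | Power, SD 1.0 |
|---|---|---|---|---|
| 10% | 0.9 × 0.5 = 0.45 | about 0.50 | 96% | 94% |
| 20% | 0.8 × 0.5 = 0.40 | about 0.50 | 90% | 87% |
| 30% | 0.7 × 0.5 = 0.35 | about 0.50 | 81% | 77% |

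Check of the 20% row: 0.40 / (0.951 × √(2/120)) − 1.96 = 1.30, and Φ(1.30) = 90%.

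If half the effect is kept (r = 0.25) with p = 20%, the all-randomised effect is 0.40 + 0.2 × 0.25 = 0.45 m/s. If all of it is kept, there is no gap.

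**5. Other outcomes**

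The week-40 means of eGFR, BP and uACR lose the same people. eGFR and BP are also measured at weeks 2 to 28 (Table 2), so the readings up to stopping are on record. uACR, like cfPWV, has no scheduled interim reading. Incidence of hyperkalaemia and of renal dysfunction is different: the renal dysfunction endpoint uses the same threshold as the Table 3 renal row, so a participant stopped under that row already counts as an event, and a participant stopped for potassium has already had the hyperkalaemia.

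**The case against.** The strongest reply is that Table 3 stops only medication, that other sections speak of all participants and all subjects, that the withdrawal visit is expressly for intention-to-treat data and includes cfPWV, and that a mixed model can be run as randomised. Detailed handling of the early reading may also sit in an analysis plan that is not shown.

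Much of this limits the point, and four stronger inferences should be resisted.

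- A reader might infer that week-40 cfPWV is never taken in these participants. The passages conflict. What can be said is that no such measurement is planned for them.
- A reader might infer that intention-to-treat analysis is impossible. It can be computed, but for these participants it depends on an assumption that the data cannot test.
- A reader might infer that harm on potassium is hidden, or that a fixed share of an eGFR decline, say a third, disappears. Incident events are counted at the trigger. A share as large as a third needs the eGFR effect to persist in full after stopping, the opposite of what is assumed for cfPWV above, together with a completers-only comparison that the plan does not state.
- A reader might infer that the cfPWV benefit is overstated by 11%, 25% or 43% (0.50 divided by 0.45, 0.40 or 0.35). Those ratios follow only from the assumed stopping rates, no retained effect, and an analysis that learns nothing from those who stopped.

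The reply does not remove the core. The general wording about all participants does not say that it covers withdrawn ones. The visit offered to them is called final. cfPWV has no scheduled interim readings from which a model could learn what happened after stopping, and an analysis plan cannot recover measurements that were not taken.

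**Conclusion.** The point holds as a contradiction between the withdrawal text and Table 3 that leaves the primary outcome unplanned at week 40 for participants stopped under Table 3. The stated intention-to-treat analysis would then rely on untestable assumptions about them, with losses plausibly unequal between arms.

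The size is not known. With 10% to 30% of the spironolactone arm stopping and keeping no effect, the gap between the on-drug effect and the effect in all randomised is 0.05 to 0.15 m/s on a target of 0.5 m/s. It shrinks as more of the effect is retained. For week-40 means of eGFR, BP and uACR, the direction and size depend on reversibility and on the analysis used, and the documents do not allow a figure.

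It is worth correcting early: the trial was still recruiting when the article was submitted, and follow-up not done cannot be restored later.

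**What to change.** Reconcile the Withdrawal criteria text with Table 3, so that meeting a Table 3 criterion ends trial medication but not trial participation. The stopping criteria themselves are unchanged.

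- Invite participants who stop medication to the week-40 and week-46 assessments already scheduled, including cfPWV, BP, bloods and uACR, unless they withdraw consent to follow-up.
- Keep the visit within 7 days as a safety visit, and state that its cfPWV reading does not stand in for the week-40 value.
- State that the primary analysis uses the week-40 value of all randomised participants, on or off medication.
- Make clear that the references to all participants (Follow-up visits) and all subjects (Unblinding) include those who stopped medication.

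The cost is a protocol amendment and matching consent wording. The visits already belong to the schedule for the 240 planned participants. The expected effect will be somewhat smaller because it includes people off drug. If 20% of the spironolactone arm stop and keep no effect, power with 120 per arm is about 87% to 90%.

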The study will be coordinated by the Primary Care Clinical Research and Trials Unit (PC-CRTU), which has been fully accredited by the National Institute for Health Research (NIHR) as a trials unit at the University of Birmingham according to the current guidelines for Good Clinical Practice. The study will be monitored to confirm compliance with the protocol and the protection of patients’ rights, as detailed in the Declaration of Helsinki. Informed written consent will be obtained from all participants. The inclusion criteria are that patients must be over 18 years old and have stage 3 CKD. Patients will be excluded for any of the following criteria:

• Diabetes mellitus,

• Terminal disease or considered otherwise unsuitable by GP,

• Clinical diagnosis of chronic heart failure,

• Atrial fibrillation,

• Alcohol or drug abuse,

• Inability to comply with trial medication and follow-up,

• Documented previous hyperkalaemia or intolerance of spironolactone,

• Documented Addisonian crisis or taking fludrocortisone,

• Severe hypertension: BP ≥ 180/110 mmHg,

• Systolic BP < 120 mmHg,

• Recent acute kidney injury or hospital admission (within previous 6 weeks),

• Chronic diarrhoea,

• Urine albumin:creatinine ratio (uACR) ≥ 70 mg/mmol,

• Serum potassium ≥ 5 mEq/l on screening visit,

• Concomitant co-trimoxazole medication,

• Concomitant angiotensin-converting enzyme inhibitor and angiotensin II receptor blocker medication,

• Concomitant lithium medication,

• Concomitant warfarin medication,

• Pregnancy,

• Breastfeeding,

• Planned major surgical intervention within 46 weeks of recruitment.

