### Study assessments

#### *Blood pressure measurement*

Blood pressure will be measured using the BpTRU™ BPM-100 automated blood pressure monitor [51]. During the screening visit, six serial sitting blood pressure measurements will be taken simultaneously on both arms, to identify which arm to use for BP monitoring for all future visits. These six BP measurements will be performed via the automated machine at 1 minute intervals. Each BP reading will be recorded. The average BP reading on each arm will be derived from the mean of the second, third, fourth, fifth and sixth readings. If there is >20 mmHg difference in systolic BP or >10 mmHg difference in diastolic BP on the average BP reading between the arms, the arm with the higher reading will be selected for all future BP and Vicorder measurements. If not, the nondominant arm will be the selected measured arm. After measurement of sitting BP, postural BP will be measured after asking the participant to stand up for 1 minute from sitting position. Postural hypotension is defined as a drop of systolic BP >20 mmHg on standing. Serial sitting BpTRU BP measurements and postural BP will be repeated during each follow-up visit on weeks 2, 4, 8, 16, 28, 40 and 46.

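### A postural systolic drop above 20 mmHg triggers withdrawal in Table 3 but is not an exclusion, although it is measured at screening: the entry and withdrawal rules are not aligned

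*Protocol article*

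**What the plan says.** Three places in the protocol article bear on this.

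- **Blood pressure measurement.** The section opens with the screening session: "During the screening visit, six serial sitting blood pressure measurements will be taken simultaneously on both arms". It continues: "After measurement of sitting BP, postural BP will be measured after asking the participant to stand up for 1 minute from sitting position". It sets a threshold: "Postural hypotension is defined as a drop of systolic BP >20 mmHg on standing". It then says that "postural BP will be repeated during each follow-up visit on weeks 2, 4, 8, 16, 28, 40 and 46". Because the later measurements are repeats, a postural value exists before randomization, and the first on-treatment value comes at week 2.
- **Design, exclusion criteria.** The list is introduced with "Patients will be excluded for any of the following criteria". Its only blood pressure items are an upper limit for severe hypertension (180/110 mmHg) and "Systolic BP < 120 mmHg". There is no postural item.
- **Withdrawal criteria, Table 3, hypotension row.** "Withdraw trial medication if systolic blood pressure <100 mmHg or postural drop of systolic blood pressure >20 mmHg". The text above the table makes loss of eligibility under Table 3 a ground for withdrawal from the trial. It also offers those who withdraw a final visit, with Vicorder measurement, within 7 days of stopping medication.

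**The concern.** The threshold that defines postural hypotension at screening is the same one that ends treatment later, but it has no role in deciding who enters. As written, someone with a standing drop above 20 mmHg at screening is eligible, is randomized, and already satisfies a withdrawal rule before the first tablet.

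If the drop is present again at week 2, that person stops trial medication whether on spironolactone or placebo. The event would be recorded under hypotension although it predates treatment.

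What is at stake is mainly the descriptive yield of the pilot. The abstract names overall tolerability as a secondary endpoint, and the Endpoints section lists the incidence of other adverse events. Early withdrawals of this kind would raise those rates in both arms, reduce treatment exposure and take a share of the drop-out allowance. A future definitive trial planned on these rates would inherit the distortion.

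**Working it through.** **Step 1. Compare entry and withdrawal rules across Table 3.**

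| Measure | Entry rule | Withdrawal rule | Can a participant enter already meeting it? |
|---|---|---|---|
| Systolic BP | excluded below 120 mmHg | below 100 mmHg | No, on the screening value |
| Potassium | excluded at 5 mEq/l or more | 6 mEq/l or more, on repeat sampling | No, on the screening value |
| Renal function | stage 3 CKD | change from baseline in creatinine or eGFR | No, the rule is relative |
| Postural systolic drop | none | above 20 mmHg, absolute, single reading | **Yes** |

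Of these four, only the postural rule has neither a margin between entry and withdrawal nor a reference to baseline.

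**Step 2. The plan's own sample-size figures.** Inputs from the sample size section: difference 0.5 m/s, SD of change 1.0 (active) and 0.9 (control), 100 completers per arm, alpha 0.05 (taken as two-sided), stated power 90%, 240 recruited, about 20% drop-out.

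Power = Φ(δ / (SD·√(2/n)) − 1.96).

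- SD 1.0, n = 100: 0.5/0.1414 − 1.96 = 1.576, so power is 94.2%.
- Pooled SD √((1.0² + 0.9²)/2) = 0.951: power is about 96%.

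The stated 90% is therefore conservative. I use SD 1.0 below.

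Losses that still leave 200 completers: 240 − 200 = 40, or 16.7% of 240. A literal 20% of 240 is 48, which would leave 192. I use 40, because it matches the stated 200 completers.

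**Step 3. Illustrative counts.** The documents give no prevalence of a drop above 20 mmHg at screening, so 5%, 10% and 15% are assumptions. The counts are upper bounds for each assumed prevalence, because they suppose that every screening drop recurs on treatment and leads to withdrawal.

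- 5%: 240 × 0.05 = 12; 12/40 = 30%
- 10%: 240 × 0.10 = 24; 24/40 = 60%
- 15%: 240 × 0.15 = 36; 36/40 = 90%

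**Step 4. Consequence for power (SD 1.0, two-sided).**

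- *A: all lost to analysis, plus 20% other drop-out.* Completers per arm = (240 − count) × 0.80 / 2.
- *B: all lost, plus 16.7% other drop-out.* Completers per arm = (240 − count) × (200/240) / 2.
- *C: all kept in the intention-to-treat analysis but off drug.* 100 per arm, with the effect diluted to 0.5 × (1 − prevalence).

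| Assumed prevalence | A: n per arm, power | B: n per arm, power | C: effect, power |
|---|---|---|---|
| 5% | 91.2, 92.2% | 95, 93.1% | 0.475, 91.9% |
| 10% | 86.4, 90.8% | 90, 91.8% | 0.450, 88.9% |
| 15% | 81.6, 89.1% | 85, 90.3% | 0.425, 85.2% |

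Only scenario C at 15% falls well below 90%.

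**The case against.** **The passages do not contradict each other.** One governs entry and the other continuation, and neither says anything the other denies. A reader might infer a contradiction, but the text supports only a lack of alignment.

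**Table 3 may mean new-onset events.** Its column is headed as adverse effects, and the text speaks of people ceasing to be eligible. Both suggest something arising on treatment. The action text sets no such condition, however, so sites could apply the rule differently. That is itself a reason to clarify it.

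**The GP can exclude unsuitable patients.** This is true, but the exclusion is discretionary and not tied to the postural reading.

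**The full protocol is not shown.** It may contain a confirmation step for blood pressure withdrawals. This is possible but not established. The article does give a repeat-sampling or two-occasion condition for potassium and sodium, and none here.

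**The trial's comparison is not damaged.** This largely stands. A pre-existing drop is expected equally in two randomized, blinded arms, so the excess adds a similar background to both. Data from withdrawn participants are collected for intention-to-treat analysis, including a final Vicorder reading. But a reading within 7 days of stopping at about week 2 cannot stand in for the 40-week change that is the primary endpoint.

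**The size is unknown.** This also stands. A single standing measurement need not recur, and the prevalence is assumed.

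**Conclusion.** The point holds as a misalignment between entry and withdrawal rules. A participant can be randomized while already meeting the postural criterion and, if the drop recurs, can be withdrawn as early as week 2 in either arm for a reason unrelated to treatment. The effect falls on crude hypotension, intolerance and withdrawal rates, on treatment exposure and on the drop-out allowance.

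Three stronger readings are tempting and not supported. The documents do not show that any given number will be withdrawn: 12, 24 or 36 of 240 are upper bounds that rest on an assumed prevalence and on full recurrence. They do not show bias between the arms. They do not show an underpowered trial: the sample size has some slack, and power stays near the planned 90% unless prevalence is high and those affected are analysed off drug. The reason to act is the quality of the pilot's tolerability and withdrawal estimates, together with a remedy that needs no new measurement.

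**What to change.** Reconcile the exclusion criteria, the blood pressure measurement section and the hypotension row of Table 3, so that nobody is randomized while already meeting the postural withdrawal criterion on the screening measurement. Which passage changes, and how, is for the clinical investigators; no threshold or rule is proposed here.

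In the tolerability results, use the recorded screening value to report withdrawals with a pre-existing drop separately from those without, by arm. This can also be done for participants randomized before any amendment.

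The cost is a short amendment through the approval route described under Design, while recruitment is still open according to Trial status. No extra data collection is needed. The possible downside is a slightly smaller eligible pool, depending on which passage is changed.
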